#### Tobacco Abstinence

Tobacco abstinence will be defined as biochemically confirmed 7-day point prevalence, which is the self-report of no smoking in the past 7 days combined with a CO reading of <6 ppm. Self-reports of smoking status will be collected via the timeline follow back at visits 2-5.

#### Analytic Plan

Descriptive statistics (eg, means and percentages) will be derived for feasibility and acceptability outcomes. Given that this is a feasibility study, sensor-driven analyses will be exploratory with the goal of providing preliminary results. The unit of analysis is the pre/postengagement data pairs comparing the average negative affect, self-regulatory capacity, and lapse counts within a prespecified time frame (eg, negative affect and self-regulatory capacity in the 30 minutes before and after randomization and lapse status in the time period between randomization of EMIs). These data will be analyzed using a generalized linear mixed model with proper adjustment for the within-subject correlation. The model can also include indicators for the category of mindfulness strategy. Each variable pair (negative affect, self-regulatory capacity, and smoking) will be analyzed separately in a pre/postengagement comparison to determine whether the mindfulness intervention creates any changes in these variables when compared with receiving no strategy at all. Examples of potential time-invariant covariates that will be included in the model are gender, age, education level, baseline trait mindfulness, and nicotine dependence. Time-varying covariates to be considered in the models include smoking status and use of the *on-demand* mindfulness content. Given that MRTs require unique considerations regarding data analysis (eg, participant availability and changes in the use of the intervention over time), we will incorporate the most recent recommendations in the literature when examining the data [69,70].

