**Figure 4 figure4:**
[figure not shown]
Randomization process based on the detection of high negative affect (low negative affect, lapse, and no lapse are not represented here for simplicity purposes). R: randomization.

When considering low/high negative affect and lapse/no-lapse occasions, participants can receive up to 2 active strategies within a block (ie, they receive a mindfulness strategy or motivational message). Thus, participants can receive up to 12 active strategies per day. Other conditions are also considered for the delivery of the strategies. These include time since last EMA being at least 15 min, time since last EMI being at least 30 min, good quality data detected via sensors, no driving, phone battery level at least 10%, and no engagement in physical activity. Given the above conditions for the delivery of EMIs, we do not anticipate individuals receiving more than 6 per day, and they may even receive fewer than 6. For instance, if someone does not lapse, then no strategies are sent for that purpose. AutoSense will not send messages when it detects driving, so no messages are sent during those times.

When active strategies are sent to participants, they will receive a notification on the phone, allowing them to know that a strategy is available. They will have the option of accepting it, delaying it for 5 min, or canceling it altogether. When participants agree, they will have the option of receiving a new strategy if they do not like the first one that appears on the phone. Participants will then let the app know whether they completed the strategy, and if they indicate *yes*, they will be asked to rate how much they liked the strategy on a scale of 1 to 5 stars. If they select 1 star, then this strategy will not be shown again to the participant.

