#### On-Demand Mindfulness Content

In addition to the strategies and surveys that will be sent to a participant’s phone, participants will also have the opportunity to practice strategies on their own (ie, user-initiated). There is a mindfulness strategy button within the app that can be clicked at any time by the participant to receive a strategy. Although participants will be choosing to engage in a strategy as opposed to being sent one, the process will be similar to that described above (eg, rating the strategy). Participants will be informed at visit 1 that they can click on this button at any time. The phone also has a Mindfulness Frequently Asked Questions (FAQ) button that participants can click at any time to learn more about mindfulness. This feature contains 13 common questions about mindfulness, such as *What is mindfulness?* and *How does being aware of my thoughts relate to me quitting smoking?*

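### The Analytic Plan names pre/postengagement pairs as its unit of analysis but sets its windows around randomization; it should fix the randomization anchor and date its time-varying covariates

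*Protocol article*

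**What the plan says.** All of the relevant analysis text is in the Analytic Plan of the protocol article.

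- Unit of analysis: "The unit of analysis is the pre/postengagement data pairs". The word *postengagement* returns later in the section, in the sentence that states the comparison.
- Windows, introduced as examples in the same sentence as the unit: "negative affect and self-regulatory capacity in the 30 minutes before and after randomization" and "lapse status in the time period between randomization of EMIs".
- Purpose: "to determine whether the mindfulness intervention creates any changes in these variables when compared with receiving no strategy at all".
- Covariates: "Time-varying covariates to be considered in the models include smoking status and use of the" on-demand content. No time of measurement is given.
- Optional term: "The model can also include indicators for the category of mindfulness strategy".

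Two other sections show what engagement is. Under Intervention Components, EMIs, a participant who is sent a strategy gets a notification: "They will have the option of accepting it, delaying it for 5 min, or canceling it altogether". Those who accept may ask for a different strategy and then report whether they completed it. Under On-Demand Mindfulness Content: "There is a mindfulness strategy button within the app that can be clicked at any time by the participant".

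**The concern.** A microrandomized trial gets its causal interpretation from the assignment at each decision point. Engagement comes after that assignment, is the participant's choice, and can occur only where a strategy was sent. A pair formed before and after engagement therefore has no counterpart at a no-strategy moment. To complete the comparison, the analyst would have to set self-selected strategy moments against all no-strategy moments. If people tend to open a strategy when they are calmer, or when they are more distressed, that contrast differs from zero even when the strategy does nothing.

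The covariates raise a related question. On-demand use can be a reaction to having received, or not received, a strategy. Smoking is one of the three variables analysed as outcomes. If either is measured after the randomization in question, adjusting for it can remove part of the effect or induce an association.

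This is the only analysis described in the article that uses the microrandomization, and its stated question is causal.

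**Working it through.** The article gives no effect size, SD or power for this analysis, so there is no figure to reproduce. The check compares the texts and then sizes the readings they allow.

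**Step 1. The two anchors side by side.**

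| Feature | Anchor = randomization | Anchor = engagement |
|---|---|---|
| Exists at strategy moments | yes | only if accepted |
| Exists at no-strategy moments | yes | no |
| Decided by | the 1:1 algorithm | the participant, after assignment |
| Stated as | example windows | unit of analysis and comparison |

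The anchors coincide only if every strategy is opened at once. The article does not expect this: it allows delay and cancellation, and its benchmark under Feasibility Outcomes is at least 60% of strategies completed. Up to 40% could go uncompleted with the target met.

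**Step 2. Bias of an engaged-only contrast.** Let p be the proportion of sent strategies engaged with. Let d be the difference in post-window mean between moments when the participant would engage and moments when they would not, with no strategy effect. Randomization makes no-strategy moments a mixture of both kinds, with mean p·m₁ + (1 − p)·m₀. Engaged moments have mean m₁. The contrast is

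m₁ − [p·m₁ + (1 − p)·m₀] = (1 − p)(m₁ − m₀) = (1 − p)·d.

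With p = 0.60 this is 0.4·d. The range for d is an assumption:

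- d = 0.1 SD: bias 0.04 SD
- d = 0.5 SD: bias 0.20 SD

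The sign follows the sign of d.

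**Step 3. Simulation with a true effect of zero.** Every association below is an assumption. There were 24 participants, 168 moments each, 1:1 assignment, 200 replicates and a within-person regression, which is simpler than the mixed model in the plan.

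- Outcome = 0.5 × person effect + 0.4 × pre-window value + 0.5 × unmeasured momentary state + noise of SD 0.7. The within-person SD is √(0.16 + 0.25 + 0.49) = 0.95.
- Log-odds of engaging = 0.405 − k × state − 0.25 × pre-window value, giving about 60% engaged.
- For covariates measured after randomization, the log-odds rise by k per unit of state and fall by 1 when a strategy is sent.

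Mean estimates, in outcome units (the truth is 0):

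| Analysis | k = 0 | k = 0.25 | k = 0.5 | k = 1.0 |
|---|---|---|---|---|
| All moments as assigned | 0.000 | −0.001 | 0.000 | −0.001 |
| As assigned + on-demand use before randomization | 0.000 | −0.001 | 0.000 | −0.001 |
| Engaged vs none, adjusted for pre value | 0.000 | −0.051 | −0.097 | −0.173 |
| As assigned + on-demand use after randomization | 0.000 | 0.008 | 0.018 | 0.037 |
| As assigned + smoking after randomization | 0.000 | 0.005 | 0.012 | 0.026 |

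The Monte Carlo error is at most about 0.035/√200 = 0.0025. When the sent strategy does not affect the later covariates (k = 0.5), both covariate rows return −0.001.

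The choice of anchor therefore matters more than covariate timing here. Adjusting for the pre-window value does not remove the engaged-only bias when the state that drives engagement is unmeasured. Analysis as assigned, with or without a covariate fixed beforehand, shows no bias.

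**The case against.** The best defence is that *engagement* is a loose label. Every concrete window in the section is tied to randomization and none to engagement. The comparator is receiving no strategy, which matches the assignment described under EMIs. Because no-strategy moments have no engagement time, the literal reading cannot be carried out in both arms, which suggests it was not meant. The authors also say the analysis is exploratory, recognise issues specific to microrandomized trials and promise to follow current recommendations.

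Much of this stands. A reader might infer that the planned model definitely conditions on behaviour after randomization, or that cancelled strategies are excluded. The article says neither. The covariates are only to be considered. Smoking status helps trigger the decision point and is monitored every minute, so it can be taken before assignment as a proper covariate; on-demand use can be taken from an earlier window.

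The defence does not remove the contradiction. The windows are only examples, while the engagement wording defines the unit and recurs in the statement of the comparison. The promise to follow the literature gives availability and changing use of the intervention as its examples; it does not say that moments are analysed as assigned or when covariates are measured. Covariate lags alone could be left to an analysis plan, but an anchor stated in two incompatible ways needs correcting where it stands.

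**Conclusion.** The contradiction is real and leaves open which moments enter the model. Under the randomization reading the contrast is sound. Under an engaged-only reading it is not randomized, with a bias of 0.4·d: 0.04 to 0.20 SD for d between 0.1 and 0.5 SD and completion at exactly 60%. The simulation gave spurious effects up to −0.173 outcome units (0.173/0.95 = 0.18 within-person SD) under its assumed associations. Covariates measured after randomization added at most 0.037 units, and essentially nothing if assignment does not affect them.

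These sizes describe what the wording permits. They do not describe an analysis the article commits to, and it would go too far to conclude that the planned contrast has lost its randomization. Severity is moderate: the analysis is exploratory, the primary feasibility outcomes are unaffected, and the authors leave efficacy to a later trial.

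**What to change.** In the Analytic Plan, or in the statistical analysis plan or a dated addendum before analysis:

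1. Replace *pre/postengagement* with *pre/postrandomization* in both places.
2. Form the windows around the randomization time in both arms.
3. Analyse every available randomized moment as assigned, whether or not the strategy was opened, delayed, cancelled or completed.
4. Use only time-varying covariates measured before that decision point, such as smoking status and on-demand use in a preceding window.
5. Label any engaged-only comparison, and any comparison by strategy category, as secondary and non-randomized. Participants can swap the strategy they are shown, so its category is partly their choice.

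This changes wording only and needs no new data; the Results section reports that data management was still under way. The price is that the estimated effect may be smaller, because unopened and uncompleted strategies stay in the strategy arm. It then estimates the effect of sending a strategy, which is what was randomized.

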### Microrandomized Trials

This study uses a microrandomized trial (MRT) design to deliver mindfulness strategies (referred to as ecological momentary interventions [EMIs]) to participants on a smartphone at key moments during a quit attempt. Using MRTs is an innovative way to investigate whether certain intervention components, when delivered at certain times, impact hypothesized mechanisms and behavior [33]. We are specifically interested in the impact of these EMIs in relation to negative affect and lapse [4,6,34-37]. Thus, during a quit attempt, moments will be randomized to either receive a strategy or not, based on (1) times of low and high negative affect and (2) smoking status (lapse and no lapse). Negative affect and smoking status will be detected unobtrusively via wearable wireless sensors, and EMIs will be delivered via smartphones.

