The day is separated into six 2-hour blocks for the delivery of EMIs. The decision point for randomization (ie, to send an active strategy or not) is based on smoking status and negative affect, both of which are being continuously monitored every minute while the equipment is being worn. For high negative affect, the decision to randomize is made as soon as a high negative affect event is detected within a 2-hour block and the participant is available. For lapse (ie, the detection of smoking), the decision to randomize is also made as soon as smoking is detected within the 2-hour block and the participant is available. Within a 2-hour block, this process is limited to one randomization occasion for high negative affect and one randomization occasion for lapse. For low negative affect, the decision point to randomize is randomly chosen at the start of the block, and if available when that time arrives, randomization occurs. If the participant is not available, another time is randomly chosen within that time block, and when that time arrives, assuming the participant is available, randomization occurs. This pattern is repeated until the end of the block. The process for randomization for no lapse is identical to the process of low negative affect, as previously described. Within a 2-hour block, randomization is limited to one occasion for low negative affect and one occasion for no lapse. In summary, up to 4 randomizations can occur within a 2-hour block (high negative affect, lapse, low negative affect, and no lapse). Moments will be randomized to receive a strategy or not in a 1:1 manner, and factors to ensure this 1:1 randomization will be included in the algorithm (ie, inclusion of historical data of what has already been triggered that day). Figure 4 shows the process of randomization based on the detection of high negative affect (low negative affect, lapse, and no lapse processes are not included in the figure for simplicity purposes, but their procedures mimic what is shown for high negative affect).

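### The example lapse window runs from one randomization to the next, so if the post-strategy lock-out or the per-block cap delays randomization, time at risk is longer after a strategy and a null strategy looks harmful

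*Protocol article*

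**What the plan says.** The Analytic Plan compares each sensor outcome after a randomized strategy with the same outcome "when compared with receiving no strategy at all". The examples of time frames are "negative affect and self-regulatory capacity in the 30 minutes before and after randomization" and, for smoking, "lapse status in the time period between randomization of EMIs". No other lapse window is given. The sentence refers both to lapse counts and to lapse status, and does not say whether a lapse that ends an interval is counted in it. The model is a "generalized linear mixed model with proper adjustment for the within-subject correlation"; no exposure offset is mentioned.

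The EMIs section sets the timing rules. "Moments will be randomized to receive a strategy or not in a 1:1 manner", provided that the participant is available. For lapse, "the decision to randomize is also made as soon as smoking is detected within the 2-hour block", again subject to availability and at most once per block. Later in the section, the conditions for delivering a strategy include "time since last EMI being at least 30 min", at least 15 minutes since the last EMA, and at most two active strategies per block. The Microrandomized Trials section uses the term EMI for the strategy itself. The section on EMAs says that half of EMIs are followed by an EMA.

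**The concern.** A comparison of lapse between arms needs the same time at risk in both. The waits after an EMI, and after an EMA that follows an EMI, are started by a strategy and not by a no-strategy assignment. Only strategies use up the cap. If these limits delay the next randomization, the interval after a strategy is longer and has more room for a lapse, whatever the strategy does. Reduced lapsing is one of the three exploratory hypotheses in Study Aims, and the bias runs against it: it could hide a benefit or suggest harm in data meant to show whether the approach warrants further study.

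A random effect for participant does not equalize time at risk. Nor does the pre/post pairing: under simple 1:1 allocation the preceding interval is complete before the arm is drawn, so it cannot offset a longer interval afterwards.

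**Working it through.** The plan gives no figure on this point to reproduce, so the check simulates the stated rules with a strategy that has no effect.

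**Inputs from the article:** six 2-hour blocks; four types of decision point, each at most once per block; 1:1 allocation; 30 minutes since the last EMI; 15 minutes since the last EMA; an EMA after 50% of EMIs; at most two strategies per block; a detected lapse triggers randomization if the participant is available.

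**Assumptions, since the article gives no rates:** lapses at 0.1, 0.25, 0.5 or 1 per hour, unrelated to arm; high negative affect at 0.5 per hour; independent 1:1 draws (the article adds an unspecified history-based balancing); 4,000 person-days per scenario.

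**Step 1. Waits and cap both gate randomization; the terminating lapse is counted.** Strategy vs none:

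| Lapses/h | Mean interval, min | Length ratio | Mean count ratio | P(any lapse) | Odds ratio |
|---|---|---|---|---|---|
| 0.1 | 58.8 vs 36.7 | 1.60 | 1.59 | 0.097 vs 0.063 | 1.59 |
| 0.25 | 57.6 vs 33.8 | 1.70 | 1.68 | 0.220 vs 0.142 | 1.70 |
| 0.5 | 56.3 vs 30.8 | 1.83 | 1.78 | 0.384 vs 0.249 | 1.89 |
| 1 | 54.6 vs 28.1 | 1.94 | 1.90 | 0.611 vs 0.395 | 2.41 |

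Odds ratio = [p1/(1 − p1)] / [p0/(1 − p0)]. At 0.25 per hour: (0.220/0.780)/(0.142/0.858) = 0.282/0.166 = 1.70. The tabled values use unrounded probabilities.

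**Step 2. Hand check.** With the terminating lapse counted, expected lapses = hourly rate × mean minutes / 60. At 0.25 per hour: 0.25 × 57.6/60 = 0.240 against 0.25 × 33.8/60 = 0.141, ratio 1.70, close to the simulated 1.68. In every row the count ratio follows the length ratio. Unequal time at risk accounts for the excess.

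**Step 3. Other readings of the rules.**

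| What delays randomization | Null odds ratio |
|---|---|
| Waits, without the cap | 1.44 to 2.03 |
| Waits and cap, triggers held until available | 1.44 to 2.34 |
| Cap only | 1.19 to 1.40 |
| Neither | 0.96 to 1.04 |

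Raising high negative affect to 2 per hour, with lapse at 0.25 per hour and the Step 1 rules, gave 1.83. Simulations with other assumed rates gave 1.38 to 1.64 (lapse 1 to 4 per 12-hour day) and 1.6 to 1.95 with the lock-out gating randomization, and 1.14 to 1.32 with only the cap.

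**Step 4. Role of lapse-triggered randomization.** A lapse that closes its own interval and is counted scores that interval as positive whether or not it closes it. Removing the trigger barely changed the odds ratio for binary lapse status. If the terminating lapse is not counted, the Step 1 odds ratios become 14.3, 7.3, 4.9 and 4.1.

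**Step 5. Alternatives.** Mean lapses in a fixed 30-minute window after randomization, strategy vs none: 0.049 vs 0.049, 0.119 vs 0.120, 0.242 vs 0.244, 0.482 vs 0.487. A fixed 60-minute window, at 1 to 4 lapses per 12-hour day, gave odds ratios of 1.03, 1.02 and 1.00. Keeping the variable interval but analyzing lapses per hour, at 0.25 per hour, gave 0.253 vs 0.257 with the terminating lapse counted and 0.148 vs 0.040 without it.

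**The case against.** The strongest objection is that the article words the 30-minute rule and the other conditions as conditions for delivery, and never says that they define availability for randomization. It also allows up to four randomizations per block but only two strategies, which is compatible with a cap on delivery alone. If neither limit delays randomization, there is no bias. This stands as a limit on the point. Against it, randomization depends on availability, and these conditions are the only ones from which availability could be built. If they did not gate randomization, some moments assigned a strategy could not receive one, which fits poorly with allocating moments to receive a strategy or not.

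The window is also only an example, for an outcome declared exploratory in a small sample, and the plan promises to follow current recommendations on participant availability. That bears on severity. It does not replace the only lapse window named.

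A reader might infer that no modeling could remove the bias. The documents do not support that: a generalized linear mixed model for counts can carry a person-time offset, and Step 5 shows that this nearly removes the bias when the terminating lapse is counted. The article's silence on an offset is no fault in itself, since an analysis plan may supply it. A reader might also infer that lapses cutting intervals short cause the distortion. For binary lapse status they are not the main driver, and the trigger acts at most once per block.

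**Conclusion.** The point holds conditionally. If the post-strategy wait gates randomization, the stated lapse window gives a null odds ratio of about 1.4 to 2.4 against the strategy; if only the cap does, about 1.1 to 1.4; if neither does, about 1.0. The direction was the same at every assumed rate when the wait or the cap applied. The size rests on assumed lapse and negative-affect rates and on independent 1:1 draws. Further distortion arises if the terminating lapse is not counted, which the article leaves open.

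It would go too far to say that the lapse analysis will certainly show spurious harm: the article does not settle which limits gate randomization, and the window is an example. This should be fixed before the lapse data are analyzed, but it does not threaten the trial's main purpose. Retention, adherence, usability and acceptability do not use this window.

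**What to change.** Replace the between-randomization interval with a fixed window of equal length in both arms that starts at randomization: for example 30 minutes, matching the other two sensor outcomes, or 60 minutes. Do not close it at later randomizations. Use observed sensor-on time in the window as an offset. State also which conditions defined availability for randomization as the system was run, so that readers can see which case above applies.

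The wording change is short and needs no new data, because smoking is monitored continuously while the sensors are worn. There is an analytic cost. Windows may overlap, so standard errors must be cluster-robust by participant. Later strategies can fall inside a window, possibly more often after a no-strategy moment. The estimate is then a proximal effect averaged over later assignments, unless those are handled by weighting, and the plan should say which is intended.
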